6.1. In what language(s) will they be fluent?

Shona.

6.2. Translation of documents into another language. Federal regulations require that consent, assent, and authorization documents must be presented to participants in a language that is understandable to them. The UW IRB expects that translated documents will be:

- Linguistically accurate;
- At an appropriate reading level for the subject population; and
- Culturally sensitive for the locale in which they will be used.

Describe how you will obtain translations of relevant documents, and how you will ensure that the translations meet these requirements.

All documentation will be drafted in English and translated by bilingual study staff. Consent forms, advertisements, and study information materials will be translated by the local study team. Interviewer-administered forms will be used in English, as used in previous studies under the Zimbabwean protocol. Trained interviewers translate orally from English to Shona and complete forms in English. All study forms will be completed in English by study staff.

6.3. Interpretation. Describe how you will provide interpretation, and when. Specifically:

1. For what situations will you provide interpretation? (At a minimum, an interpreter should be available for the consent process, unless the IRB has waived consent.)

The study will not use any interpreters.

1. Who will be the interpreter?

1. Describe the qualifications of the interpreter – for example, background, experience, language proficiency in English and in the other language, native language fluency, certification, other credentials, familiarity with the research-related vocabulary in English and the target language.

1. How will you ensure that the subjects will understand ongoing study-related communication? If the subject has questions, complaints, or adverse events, how will that be communicated to the researchers?

*Check all that apply:*

**Written** *Attach copies of all consent forms for each subject group. Include a footer identifying the version date of each form and a header or title that identifies each different form. If you propose to delete one or more of the required elements of consent from a consent form, attach and complete the form called* [*Waiver Request: Consent or Consent Requirements*](http://www.washington.edu/research/link.php?id=1595)*.*

**Waiver of written documentation of consent** *This means that you are requesting a waiver of the requirement to obtain written documentation of consent. Complete and attach the form called* [*Waiver Request: Consent or Consent Requirements*](http://www.washington.edu/research/link.php?id=1595)*. Also, attach the Information Statement, oral consent or assent protocol and script, or other materials you will use to communicate the necessary elements of consent to the subjects.*

**Waiver of consent** *This means that you are requesting a waiver of the requirement to obtain consent. Complete and attach the form called* [*Waiver Request: Consent or Consent Requirements*](http://www.washington.edu/research/link.php?id=1595)*.*

**Assent** *Attach copies of any written materials or scripts you will use with minor subjects (individuals under the age of 18) to obtain their assent to being in your research.*

**Parental permission** *Attach copies of any written materials or scripts you will use with parents, to obtain their permission to enroll their minor children in your research. See also* [*Supplement: Protected and/or Vulnerable Populations*](http://www.washington.edu/research/hsd/docs/322) *for waivers or alterations of consent requirements.*

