Individual interviews will be conducted by trained psychosocial interviewers to collect data from HIV-infected participants on satisfaction with the PrePex™ MC procedure, attitudes towards MC, compliance with instructions to refrain from sexual intercourse for 7 weeks post placement [(Day 49 or 6 weeks post removal) or until a clinician tells them that they are fully healed – whichever is later], barriers and motivators to uptake of VMMC through PrePex™, opinions around convenience of the device, tolerance of potential odour and whether participants would recommend PrePex™ MC to others. The interviews with same participants will be held at three points in time: prior to the procedure, two weeks post-procedure, and 90 days post-procedure (Appendices 6-8). In addition all health care providers at facilities where PrePex™ circumcision is offered will be interviewed on the acceptability of the PrePex™ procedure for HIV-infected clients. Interviews with providers (Appendix 9) will take place at one time point approximately 4 weeks post study initiation.

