**Patient interviews:**

For the interviews, up to 103 men who get circumcised and consent will be randomly selected to have a private *face-to-face interview* at three points in time: prior to their procedure, 14 days and 90 days after procedure. Interviewer administered questionnaires will be used to collect required data.

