**Data Collection**

Overview table:

| Study Objective | Sample Size Est. | Sampling method | Data collection Methods | Tools |
| --- | --- | --- | --- | --- |
| 1.1.1 (Safety) | 400 | Purposive | Interview | CRF |
| 1.2.1 (Level of care) | 400 | Purposive | Interview  Observation | CRF |
| 1.2.2 (Acceptability) |  |  |  |  |
| Clients | 103 | Random | Interview | QES |
| Providers | All | Purposive | Interview | QES |
| 1.2.3 (Facilitators/Barriers) |  |  |  |  |
| Clients | 103 | Random | Interview | QES |
| Providers | All | Purposive | Interview | QES |
| 1.2.4 (Compliance with instructions) | 103 | Purposive | Interview | QES |
| 1.2.5 (AE monitoring) | 400 | Purposive | Interview  Observation | CRF |

If you are the direct recipient of federal funding for this project and other organizations are “engaged” in the research (see the Worksheet on Engagement), you are responsible for obtaining IRB approval from the other organizations or for requesting that the UW conduct the IRB review on behalf of that organization. See the document [SOP Research Collaborations or Multiple Performance Sites](http://www.washington.edu/research/hsd/docs/1644) and [WORKSHEET IRB Review Options](http://www.washington.edu/research/hsd/docs/1645) for more information.

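### Participant questionnaires stay in English and are put into Shona orally by each interviewer, with no agreed Shona wording described for three secondary interview outcomes

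*Protocol*

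**What the plan says.** Section I (Consent), item 6.1 names Shona as the language in which participants will be fluent. Item 6.2 then makes four statements about translation:

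- In general: "All documentation will be drafted in English and translated by bilingual study staff".
- Documents named for translation: "Consent forms, advertisements, and study information materials will be translated by the local study team". Questionnaires are not in this list.
- Interview forms: "Interviewer-administered forms will be used in English, as used in previous studies under the Zimbabwean protocol".
- How an English form reaches a Shona speaker: "Trained interviewers translate orally from English to Shona and complete forms in English".

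Item 6.3 adds that no interpreters will be used.

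The participant questionnaires fall under the third and fourth statements. The paragraph on patient interviews in Section B says: "Interviewer administered questionnaires will be used to collect required data". It also says that "up to 103 men who get circumcised and consent will be randomly selected to have a private" interview. The Psychosocial Component adds: "The interviews with same participants will be held at three points in time", namely before the procedure, at two weeks and at 90 days.

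The overview table under Data Collection takes client acceptability and client facilitators/barriers from the questionnaire in 103 men. Its abstinence row reads "1.2.4 (Compliance with instructions) | 103 | Purposive | Interview | QES".

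**The concern.** A questionnaire measures the same thing in every man only if every man is asked the same question. Under item 6.2 the fixed text is English, while the question a Shona speaker hears is whatever Shona the interviewer produces. Two interviewers may render one item differently, and one wording used by all may carry a meaning the English item did not intend. The answer is then put back into English as it is written down.

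This matters most for abstinence. The secondary objectives treat compliance with that instruction as a public health safety matter, and it is self-reported. The background section already treats resumption of sex before healing as hard to measure. It cites 1.1% and 15.7% from two studies and regards the first as too low and the second as too high because of the methods used. Those remarks are not about translation, but they show that the answer depends on how it is obtained.

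Item 6.2 of the form asks how translations will be made accurate and culturally suitable. For the oral translation, the protocol answers only that interviewers are trained and that earlier studies used the forms this way.

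**Working it through.** The protocol states no figure on this point, so the check is a comparison of its sections.

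1. **Does oral translation apply to the participant questionnaires?** Yes. Item 6.2 applies it to interviewer-administered forms, and Section B describes the patient questionnaires in those terms. It affects men interviewed in Shona; a man interviewed in English hears the form as written.

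2. **Does the general sentence in item 6.2 override this?** It says all documentation is translated, which could cover the questionnaires. The sentences after it are more specific. They list consent forms, advertisements and information materials for translation, and say that the interview forms are used in English. The specific sentences govern, but read literally the two statements conflict.

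3. **Does the protocol describe an agreed wording elsewhere?** No. Item 6.2 mentions no agreed Shona text and no back-translation. The recordings in Section H, item 6 cover the procedure and photographs of the penis; no interview recording is described. The operating procedures (Appendix 3) and questionnaires (Appendices 6-8) are listed but not shown, so this step concerns the protocol text only.

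4. **Which outcomes depend on these interviews?** Client acceptability, client facilitators/barriers and abstinence compliance, from the Data Collection table and the Psychosocial Component. All are secondary.

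5. **Is the primary endpoint exposed?** Largely not. The Data Collection table does list interview as the method for safety. However, the visit descriptions in Section B have a clinician examine the participant and record adverse events on the case report form at the removal and follow-up visits.

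6. **Can the effect be sized?** No. For variation between interviewers the usual expression is a design effect, 1 + (m - 1) x ICC. Here m is the number of men per interviewer and ICC is the intraclass correlation of answers within interviewer. The protocol gives n = 103 but neither the number of interviewers nor an ICC. A shift in meaning shared by all interviewers is bias, and this expression does not capture it.

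**The case against.** The best defence is that the practice may be more controlled than item 6.2 shows. Interviewers are trained, and the method is carried over from previous Zimbabwean studies. An agreed Shona phrasing could be taught in training, set out in the operating procedures or written on the forms, and the forms may already identify the interviewer. This stands in part. A reader may not conclude that the wording is in fact unagreed or unrecorded, only that the protocol describes no agreed wording and fixes the forms in English.

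Three stronger readings are tempting, and the protocol does not support them.

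- **A stated loss of precision.** One could assume a number of interviewers and an ICC and report a wider confidence interval. Both inputs would be invented. The ICC would also include rapport, probing and reluctance to discuss sex, most of which a written Shona version would leave in place.
- **False change between visits.** The protocol plans no analysis of change in interview answers. The three questionnaires are separate appendices, so repeated items cannot be confirmed. Abstinence after the procedure cannot be asked before it.
- **Lost comparability with earlier studies.** The mention of previous studies describes established practice. The comparison with earlier Zimbabwean data is planned under the Clinical Component and is not claimed for interview results.

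It is also fair to say that only secondary, self-reported objectives are involved. That limits the importance of the point but does not answer it.

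**Conclusion.** The point holds as a minor, inexpensive improvement. The protocol fixes oral translation by the interviewer as the way Shona speakers receive the questionnaires and describes no agreed Shona wording. A sentence in the same item says the opposite if taken literally. Answers on acceptability, facilitators/barriers and abstinence, from up to 103 men, can therefore vary with the interviewer's wording or shift in meaning.

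No numerical size is attached, because the protocol does not give the inputs. The conclusion assumes that at least some interviews are held in Shona, which follows from item 6.1, and that the unseen appendices do not already supply the wording. If they do, only the conflict between the two sentences remains.

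**What to change.** Amend Section I, item 6.2 as follows:

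- Administer the three participant questionnaires (Appendices 6-8) to Shona speakers from one agreed written Shona version, used by all interviewers.
- Have that version prepared by the local team already translating the consent forms and checked by a second bilingual staff member.
- Continue to record answers in English.
- Identify the interviewer on each form, if this is not already done.
- Reword the general sentence on translation so that it agrees with the sentence on interview forms.

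If an agreed Shona wording already exists in the training material or appendices, a sentence in item 6.2 saying so, together with the reconciliation, is enough.

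The cost is some one-time preparation before interviews begin. The forms are not shown, so the amount cannot be stated more closely. The procedure, the visit schedule and the English records stay as they are.

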**J. DRUGS, SUBSTANCES, AND DEVICES**

1. List **all** non-investigational drugs or other substances used to conduct this research (analgesics, anesthetics, drugs used to treat side effects, etc.). Include products used for standard clinical care if they are used in this study for research purposes.

| Name | Source | Dose | How administered |
| --- | --- | --- | --- |
| Ibuprofen | ZiCHIRe will source locally | 400 mg | Oral |
| Lidocaine | ZiCHIRe will source locally | 5% dermal cream | Topical |
| Cloxacillin | ZiCHIRe will source locally | 250 mg | Oral |
| Ciprofloxacin | ZiCHIRe will source locally | 500 mg | Oral |
| Paracetamol | ZiCHIRe will source locally | 500 mg | Oral |

2. List **all** investigational new drugs or other investigational substances to be used in the study. Include marketed products used “off-label” (different formulation, dose, route of administration, or indication). Provide:

1. **three** copies of a concise summary of information about the drug prepared by the investigator (including animal and human toxicity data, studies done in animals and humans to date);
2. **one** copy of the Investigator’s Brochure;
3. **one** copy of the study protocol.

**Important note**: You must register an IND with the appropriate institutional pharmacy (**UWMC: [name]; HMC: [name],
VA: [name]**) before using the drug in research.

| Name | Source | Dose | How administered | IND Number | Phase of testing |
| --- | --- | --- | --- | --- | --- |
|  |  |  |  |  |  |
|  |  |  |  |  |  |
|  |  |  |  |  |  |
|  |  |  |  |  |  |

3. List all investigational devices you will use. Provide the information requested below and attach one copy of the company protocol. If there is no Investigational Device Exemption (IDE), explain why. Include a statement as to why the device qualifies as non-significant risk. Provide a copy of the FDA letter(s) which states the device classification (PMA, 510K, Class I, II, or II, or custom device) and categorization (Category A or B). “Category A” means that Medicare may **not** be billed for the device or for services related to its use. “Category B” means that Medicare may be billed for services related to its use **if** the U.S. Health Care Finance Administration (HCFA) grants authorization. **Important Note:** Register IDE devices with the UWMC Manager of Surgical Support Services ([name]) or the HMC Business Manager of Surgical Services ([name]) to obtain authorization for use.

a. Name of the device: PrePex™

The PrePex™ device is FDA cleared with 510(k) status (K103695; see 510(k) and is thus not considered “investigational”; however we are providing the following details for the information of the IRB review committee. The device is certified CE Mark Class IIa. It is manufactured using USP Class VI biocompatible elastomeric materials compliant to ISO_13485 Medical Devices (Quality Management systems) and FDA, 21 CFR177. 2600. Circ MedTech is ISO 13485 certified.

b. Name of the manufacturer: Circ MedTech

c. Description of its purpose and how you will use it in this study:

PrePex™is a single use, disposable device; indicated for circumcision of adult men, defined as circumferential excision of the foreskin or prepuce at or near the level of coronal sulcus, with minimal amount of preputial skin remaining.

d. Descriptions of previous studies in humans and animals:

The WHO Technical Advisory Group (TAG) on Innovations in Male Circumcision reviewed eight studies from 3 African countries in the WHO Framework for Clinical Evaluation of Devices (see WHO Pre-Qualification Report: <http://www.who.int/diagnostics_laboratory/male_circumcision/130530_pqmc_public_report_final_v1.pdf>). All studies included only healthy males 18 years and older. The device was placed successfully on 2417 eligible men. Adverse events occurred among 1.7% of participants; the majority were Mild and Moderate, while 0.4% were considered Serious as prompt surgical intervention was required to prevent serious long-term sequelae (in all cases surgical intervention was successful with no complications and satisfactory outcomes). The AE rate was lower among men who had PrePex™ circumcision than among men who had conventional surgery, but this difference was not statistically significant. No mechanical failures were reported. Healing time appears to be about 1 – 2 weeks longer than following conventional surgical circumcision. Some pain occurs with PrePex™ procedures, primarily during the first few days after placement and briefly on removal of the device. Complaints of unpleasant odor were also noted by some study participants and providers.

The WHO Technical Advisory Group (TAG) on Innovations in Male Circumcision concluded that the range and scope of clinical studies met the WHO requirements for evaluation of a device; and demonstrated that, for the purposes of HIV prevention, the PrePex™ device can efficaciously and safely circumcise healthy males over 18 years, when used by suitably trained providers, and when surgical backup facilities and skills are available to manage device displacements or early removals that could result in serious complications.

The TAG advised that: effective training materials are available and PrePex™ providers are appropriately trained; men receive accurate information on safe device use and risks while wearing a device and PrePex™ is used only in settings where suitable surgical facilities and skills are available within a short time frame (6-12 hours). This conclusion is time-limited and must be reassessed in about one year when more experience and data are generated to further inform safe use.

e. Investigational Device Exemption (IDE) number or FDA status:

WHO Prequalification Number: PQMC 0001-001-00

FDA 510(K) K103695 – Substantially Equivalent: <http://www.accessdata.fda.gov/cdrh_docs/pdf10/K103695.pdf>

Appendices:

